### 2.6. Statistics analysis

Descriptive statistics will be utilized to check for exchangeability between the two groups according to baseline variables. Non-categorical data will be presented as mean and standard deviation and analyzed using a t-test or median and inter-quartile ranges analyzed with Wilcoxon rank sum test, depending on whether the given variable follows a normal distribution. Depending on Cochran’s rule, categorical data will be presented as numbers or proportions and analyzed with either a Fisher or Chi-square test. Survival outcomes will be presented with Kaplan-Meier curves.

To assess whether interaction terms will be needed in the primary analysis, we will construct a margins plot highlighting the mean of each group at each time point (baseline, at hospital discharge, and six months after hospital discharge).

The final manuscript will report 95% confidence intervals and two-sided p-values. A p-value below 5% will be considered statistically significant.

All data will be analyzed in STATA/BE version 18 or R.

The data analyst will be blinded for group allocation during the statistical analysis.

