#### 2.3.1. Demographic variables

Demographic variables collected at baseline will include the patient’s age, sex, reason for hospital admission, and number of medications.

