### 2.4. Sample size

To calculate power, we used a Monte Carlo simulation. We based the simulation on the beta-regression [67]. We assumed the proportion of PIMs were distributed across different time points, as highlighted in Table 1, similar to results reported by McCarthy et al. [68]. The Do-File from STATA/BE used for the calculation is found in S2 File.

**Table 1 pone.0314023.t001:** *Data used for the power calculation*.

Time point	At hospital discharge	Six months after hospital discharge
Proportion of PIMs in intervention group	15%	13%
Proportion of PIMs in control group	10%	12%

Data from McCarthy et al. [68] used to calculate the sample size. Abbreviation: PIMs = Potentially Inappropriate Medication

The variance was set at 0.5, and we assumed the risk of dropout after 6 months was associated with age (see formula below)

P(dropout)=exp(1.1*age-70)/(1.1*age-70+1)
(1)

We calculated the p-value using the likelihood ratio test because we have multiple time points. Under the assumption that age will be related to the dropout rate, we needed 70 patients in each group to achieve a power of 93% at an alpha level of 0.05.

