#### 2.6.1. Primary analysis

The primary analysis will be a beta-regression with clustered standard errors as we have repeated measurements, thus adopting a population-averaged approach. We will incorporate an interaction between group and time, as we are unsure if the treatment is stable over time. Therefore, we will present the estimates for each time point (baseline, at hospital discharge, and six months after hospital discharge) and construct a margins plot based on the model. We will conduct a global test to test whether our intervention affects the primary outcome across all time points. If the test is statistically significant, we will conduct a z-test at each time point to assess when there is a statistically significant treatment effect. To avoid inflating the type I error rate in these z-test, we will adjust the z-test for multiple testing.

The primary analysis will follow the intention-to-treat principle; hence, missing data will need to be managed. As the beta regression uses maximum likelihood estimation, we can assume that the beta regression will yield unbiased results if the data is missing at random or completely at random. However, under the assumption of missing not at random, the estimates from the beta regression will be biased therefore, we will conduct joined modelling to assess the influence of missing data if the data was missing not at random. In the joint model, we will use logistic regression to estimate the risk of dropout.

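### Baseline significance tests cannot show that randomised arms are exchangeable; describe the arms instead, and prespecify age and number of medications in the primary model

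*Protocol article*

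**What the plan says.** Section 2.6 opens with the purpose of the baseline comparison: "Descriptive statistics will be utilized to check for exchangeability between the two groups according to baseline variables". The method follows at once. For continuous variables, "Non-categorical data will be presented as mean and standard deviation and analyzed using a t-test", with the Wilcoxon rank sum test as the alternative if the variable is not normal. For the others, "categorical data will be presented as numbers or proportions and analyzed with either a Fisher or Chi-square test". Later in the same section come the reporting rule, "The final manuscript will report 95% confidence intervals and two-sided p-values", and the threshold, "A p-value below 5% will be considered statistically significant". No other yardstick for balance is given, such as a standardised difference.

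The variables concerned are listed in 2.3.1: "Demographic variables collected at baseline will include the patient’s age, sex, reason for hospital admission, and number of medications". Section 2.5 plans block randomisation of 70 patients per group with variable block sizes and names no stratification factor.

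Section 2.6.1 describes the primary model as a beta regression with clustered standard errors. On its terms it says: "We will incorporate an interaction between group and time, as we are unsure if the treatment is stable over time". No covariate is named. The PIM proportion at baseline enters as one of the three modelled time points, that is, as a response with its own estimate. The same section argues that likelihood estimation gives unbiased results if data are missing at random. Section 2.4 derives the sample size "Under the assumption that age will be related to the dropout rate".

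**The concern.** Two features of the plan belong together.

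First, the tests answer the wrong question. A baseline test asks whether both arms could have been drawn from one population. Proper randomisation guarantees that they were. A small p-value is then a chance finding, and a large one says nothing about whether the patients actually enrolled are alike on what matters. A clean baseline table invites the reader to take the arms as shown to be comparable; a single starred row invites doubt about a sound randomisation.

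Second, the covariates could do real work elsewhere. As the analyses are described, the baseline table is the only use made of age, sex, reason for admission and number of medications. The protocol itself gives weight to one of them, since its power simulation makes dropout depend on age. Number of medications is, by inference, the denominator of the PIM proportion. Leaving both out of the primary model gives up precision and protection against chance imbalance. It also leaves the missing-at-random argument without the variable assumed to drive missingness.

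**Working it through.** **Inputs from the protocol article.** 70 patients per arm (2.5); two-sided 5% (2.6); four baseline variables (2.3.1). The article states no figure for the imbalance that its baseline check could detect, so there is none to reproduce.

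**1. Largest observed difference that stays non-significant.** In SD units, the standard error of a difference in means is √(2/70) = 0.169.
- Normal critical value: 1.96 × 0.169 = 0.331 SD.
- t critical value on 138 degrees of freedom: 0.334 SD.

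For a binary variable at 50% in one arm (35 of 70), the uncorrected chi-square test first gives p < 0.05 at 47 of 70 in the other arm, a difference of 12/70 = 17.1 percentage points.

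**2. False alarms when randomisation is sound.** If the four tests are treated as independent, the chance of at least one p < 0.05 is 1 − 0.95⁴ = 0.185, or 18.5%.

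**3. Precision from adjustment.** If covariates explain a share R² of the outcome variance, the standard error of the arm contrast shrinks approximately by the factor √(1 − R²). The article gives no R², so a range is assumed:
- R² = 0.10: √0.90 = 0.949, about 5% smaller.
- R² = 0.20: √0.80 = 0.894, about 11% smaller.

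**4. Overall type I error.** Under randomisation a baseline difference falls in either direction with equal probability, so the unadjusted comparison keeps its nominal level over all trials. To see whether passing the baseline test changes this, take one covariate with an assumed correlation r with the outcome. Let z_b be the standardised baseline difference and average P(|N(r·z_b, 1 − r²)| > 1.96) over |z_b| < 1.96. The result is 4.7% for r = 0.3, 4.3% for r = 0.5 and 3.5% for r = 0.7, all below 5%. This uses a single z-test, a simplification of the global test planned in 2.6.1.

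**5. Missing data, by reasoning.** A likelihood analysis is protected under missing at random only given the variables in the model. If dropout depends on age, as 2.4 assumes, and age also relates to PIMs, missingness remains tied to the outcome after conditioning on group and time alone. Putting age in the model removes that path. If age is unrelated to PIMs, this argument for including it falls away.

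**The case against.** **No decision hangs on the baseline tests.** Nothing in 2.6 to 2.6.2 selects covariates, changes the model or gates the primary test on a baseline p-value. Deleting the tests leaves the primary estimate and its error rate as they were. This stands, and it limits the harm to how the baseline table is read.

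**The decision rule is partly inferred.** The 5% level is stated for p-values in general, and the article nowhere says that non-significance will be taken as balance. That also stands. Even so, the stated purpose is to check exchangeability, tests are assigned to that purpose, and no other criterion is offered.

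**The article does not exclude covariates.** It condenses a fuller plan, and a separate analysis plan could list them. This is fair: the covariate part is an improvement to the model as described, not proof that adjustment has been ruled out. The criticism of the baseline tests rests on explicit text and does not depend on it.

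**Age and dropout are linked only in a power simulation.** That is not evidence that age predicts PIMs, which is why the missing-data argument is conditional.

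**A stronger reading to avoid.** A reader might infer that an imbalance just under 0.33 SD inflates the false-positive rate of the primary test. That would be so only in the few trials that happen to land near the limit, and only with a strong covariate-outcome correlation, for which the article gives no figure. Over all trials the level is preserved, and among trials that pass the baseline test it is slightly below 5%. A reader might likewise ask how often the tests would miss a true difference between the arms. Proper randomisation rules such population differences out, so that miss rate does not measure harm here.

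**Conclusion.** The point holds as the removal of an invalid check and a gain in efficiency and missing-data support. It is not a demonstrated failure of error control.

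- **Firm, from the text and arithmetic:** significance tests cannot establish exchangeability after randomisation. With 70 per arm they let observed differences up to about 0.33 SD pass. They raise at least one false alarm in 18.5% of sound trials, if the four variables are independent.
- **Conditional on an assumption:** the standard error would be 5% to 11% smaller if age and number of medications explain 10% to 20% of outcome variance.
- **Conditional on an unverified link:** age in the model supports the missing-at-random claim only if age relates to PIMs as well as to dropout.

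The change is worth making, but the trial's validity does not turn on it.

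**What to change.** **In 2.6:** delete the t, Wilcoxon, Fisher and chi-square tests on baseline variables, together with the wording that they check exchangeability. Present the baseline variables by arm as descriptive statistics, with standardised differences if wanted.

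**In 2.6.1:** name age and number of medications at inclusion as covariates in the primary beta regression, included whatever the baseline table shows. Report the arm contrast as a marginal difference in PIM proportion, averaged over the covariates, so that it remains population-averaged. Section 2.6.2 already plans G-computation for secondary outcomes, so this kind of step is familiar to the team. If a separate analysis plan already lists these covariates, a cross-reference is enough.

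**Cost:** wording only, to be settled before unblinding. Both variables are already collected, and no extra patients or visits are needed. The downside is two more model parameters and the standardisation step.

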#### 2.6.1. Primary analysis

The primary analysis will be a beta-regression with clustered standard errors as we have repeated measurements, thus adopting a population-averaged approach. We will incorporate an interaction between group and time, as we are unsure if the treatment is stable over time. Therefore, we will present the estimates for each time point (baseline, at hospital discharge, and six months after hospital discharge) and construct a margins plot based on the model. We will conduct a global test to test whether our intervention affects the primary outcome across all time points. If the test is statistically significant, we will conduct a z-test at each time point to assess when there is a statistically significant treatment effect. To avoid inflating the type I error rate in these z-test, we will adjust the z-test for multiple testing.

The primary analysis will follow the intention-to-treat principle; hence, missing data will need to be managed. As the beta regression uses maximum likelihood estimation, we can assume that the beta regression will yield unbiased results if the data is missing at random or completely at random. However, under the assumption of missing not at random, the estimates from the beta regression will be biased therefore, we will conduct joined modelling to assess the influence of missing data if the data was missing not at random. In the joint model, we will use logistic regression to estimate the risk of dropout.

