#### 2.6.2. Analysis of secondary outcome

As quality of life, treatment burden, and patients’ medication risk score all follow a Likert scale, we will use beta-binomial regression. The beta-binomial assumes our outcome follows a binomial distribution where the probability of landing in a given category follows a beta distribution to account for over-dispersion. As both outcomes are measured at different time points and the beta-binomial regression uses a maximum likelihood estimation, we will adopt the same test and manage missing data similarly to the primary analysis. In order to get interpretable effect sizes, we will use G-computation, where the Q-model will be a linear regression.

Our follow-up time is 30 days, so we will conduct a binomial regression to calculate the risk difference. Furthermore, we will view the above-mentioned secondary outcomes as time-to-event outcomes. Hence, we will use the Cox-proportional hazard model to ensure that our results are not dependent on the length of our study. The proportional hazard assumption will be graphically assessed using scaled Schönfeld residuals. Binomial regression is the primary analysis applied, while Cox regression is a sensitivity analysis.

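### After the 5% global test, the z-tests need neither a baseline contrast nor a further multiplicity adjustment; the adjustment only costs power to say when PIMs differ

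*Protocol article*

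**What the plan says.** Section 2.6.1 plans a beta-regression with a group-by-time interaction and a global test of whether the intervention affects the primary outcome across all time points. The time points listed are baseline, hospital discharge and six months after discharge. The second stage reads: "If the test is statistically significant, we will conduct a z-test at each time point to assess when there is a statistically significant treatment effect". The next sentence adds: "To avoid inflating the type I error rate in these z-test, we will adjust the z-test for multiple testing". The method of adjustment is not named.

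Section 2.6.2 carries the rule to the repeated secondary outcomes: "we will adopt the same test and manage missing data similarly to the primary analysis".

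On power, section 2.4 says "We calculated the p-value using the likelihood ratio test because we have multiple time points" and "we needed 70 patients in each group to achieve a power of 93% at an alpha level of 0.05". Section 2.6 sets the sidedness: "The final manuscript will report 95% confidence intervals and two-sided p-values", with 5% as the significance limit.

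**The concern.** A statement about when PIMs differ has to pass two hurdles: the global test at 5%, then a z-test at a stricter level. Two features of the second hurdle look unnecessary.

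- One of the three z-tests is at baseline. Any difference there is chance, so the test cannot support a treatment claim. If the adjustment counts it, it makes the other two tests stricter.
- Only two hypotheses about treatment remain, and for two hypotheses a global test already protects the individual tests that follow it.

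At stake is power to locate the effect. The trial could obtain a significant global test and then be unable to call discharge or six months significant, more often than error control requires.

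**Working it through.** **1. The plan's own figure.** The 93% cannot be reproduced with certainty. Section 2.4 sets the variance at 0.5 without giving its scale, and the printed dropout formula does not return a probability (at age 60 it gives −0.006, at age 70 it gives 137). If 0.5 is read as a variance on the logit scale, with independent time points and full retention:

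- discharge: logit 0.15 − logit 0.10 = 0.463; z² = 0.463² / (2 × 0.5/70) = 15.0
- six months: logit 0.13 − logit 0.12 = 0.091; z² = 0.091² / (2 × 0.5/70) = 0.6
- joint noncentrality about 15.6, giving power 95.2% on 2 df and 92.7% on 3 df

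That is near 93%, but the scale is an assumption. Below, 93% is taken as given for a joint test.

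**2. Error control without the second adjustment.** Let H1 be no difference at discharge and H2 no difference at six months. The baseline contrast is null by randomisation.

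- H1 and H2 both true: any false claim requires a significant global test, so its probability is at most 5%.
- Only one true: a false claim requires that contrast's own 5% z-test to be significant, so again at most 5%.

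This is closed testing with two hypotheses. It holds whether or not the global test also contains the baseline contrast. Simulation agrees: at most 5.0%, with either a 2-df or a 3-df global test.

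**3. What the adjustment costs.** Assumptions not in the article: Bonferroni over three tests (each at 0.05/3), a 3-df global test, and equal between-visit correlation of 0, 0.5 or 0.7. The z-statistics are drawn from a trivariate normal distribution. Two effect patterns are used:

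- *Table 1 pattern.* The gaps are |15 − 10| = 5 and |13 − 12| = 1 points, a 5:1 ratio. They are scaled so that a 2-df test of the two post-randomisation contrasts has 93% power (noncentrality 14.11).
- *Six months only.* z = 3.24, where a single 5% z-test has 90% power. This scenario is assumed.

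| Probability of the claim | corr. 0 | corr. 0.5 | corr. 0.7 |
|---|---|---|---|
| Table 1, discharge or six months: adjusted | 88% | 87% | 75% |
| Same, z-tests at 5% | 90% | 92% | 87% |
| Six-month-only effect, claim at six months: adjusted | 75% | 79% | 80% |
| Same, z-tests at 5% | 78% | 87% | 90% |
| No effect anywhere, false claim: adjusted | 2.3% | 2.1% | 1.9% |
| Same, z-tests at 5% | 3.5% | 3.1% | 2.8% |

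Cost of the adjustment under Table 1: 90 − 88 = 2, 92 − 87 = 5 and 87 − 75 = 12 points. Before rounding, the last is 86.6 − 75.4 = 11.2. For six months only, the unrounded costs are 77.5 − 75.2 = 2.3, 87.3 − 79.4 = 7.9 and 89.8 − 80.1 = 9.7 points.

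**4. The six-month claim under Table 1.** Its power is about 4 to 5% with the adjustment and about 9 to 11% without it. The assumed 13% against 12% explains this; the adjustment hardly matters.

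**5. Secondary outcomes.** Sections 2.3.3.1 and 2.3.3.4 give quality of life and treatment burden at inclusion, discharge and three months, and MERIS at inclusion and discharge. None has more than two post-randomisation time points, so step 2 applies to them as well.

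**The case against.** The strongest defence is that the rule is correct for the tests it lists. With three z-tests, the global test alone does not protect the family: if there is a large effect at discharge and none elsewhere, two null contrasts remain, and unadjusted tests would give 1 − 0.95² = 9.75% at correlation 0. So a reader who infers that the plan's reason for adjusting is wrong goes too far. This stands. The excess arises only because a baseline difference is counted as a claim, however, and it disappears once the baseline z-test is dropped.

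A reader might also infer that no treatment effect can be claimed until a z-test succeeds, and that the 93% is therefore misreported. The article does not support this. The global test asks whether there is an effect and the z-tests ask when. Section 2.4 attributes the 93% to a likelihood ratio test and never to a single time point.

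Finally, a reader might set 93% against 88%, 87% and 75% and read off a loss of 5 to 18 points. That mixes two things. The same noncentrality gives 93% on 2 df but 89.9% on 3 df, so at correlation 0 most of the gap comes from the global test. Other choices of degrees of freedom, correlation and number of tests give losses at discharge from 1.7 to 29 points. No single figure follows from the documents.

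The unnamed method could also be one that exploits the global test and costs little. That is fair, and naming it may be left to the analysis plan. The sentence proposed below would settle it.

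**Conclusion.** The point holds as a free improvement, not as an error in validity. The planned rule cannot inflate the type I error rate and biases no estimate. The baseline z-test serves no treatment claim. Without it, the adjustment of the other two buys no error control that the 5% global test does not already give.

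The adjustment costs about 2 to 12 points for a claim at discharge or six months under the Table 1 pattern, and about 2 to 10 points for a six-month-only effect with z = 3.24. Both ranges rest on assumed Bonferroni over three tests, a 3-df global test and correlations of 0 to 0.7; a less strict procedure would lose less. The closed-testing argument itself needs none of these assumptions. It needs only that each test holds its 5% level and that there are at most two post-randomisation contrasts.

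**What to change.** In section 2.6.1, remove baseline from the z-tests and replace the adjustment sentence with wording such as: *If the global test is significant at 5%, the group contrasts at hospital discharge and at six months are each tested at two-sided 5%. By the closed testing principle this controls the family-wise error rate at 5%, and no further adjustment is made.* The baseline estimate can still be shown descriptively.

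In section 2.6.2, apply the same rule to outcomes with at most two post-randomisation time points.

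Optionally, note in section 2.4 that 93% is the power of the joint likelihood ratio test, not of a claim at a given time point, and add the simulated power for each time point from the existing do-file.

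The cost is a sentence or two and, if wanted, one more output line from the simulation. No patients or data collection are needed. The change should be fixed before the data are analysed.

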Patients in both groups are included from the same ward, which might result in contamination bias [87]. The physicians treat patients from both groups and will likely adopt some medication-related learning. The physicians may apply this learning to some of the patients in the control group, resulting in an increased focus on the patient’s medication treatment. These limitations would bias the estimation of the effect towards no difference in relation to the null hypothesis.

Three questionnaires are to be answered by the patients, so there is a risk of transfer bias [88]. Patients might be particularly susceptible to loss of follow-up in Questionnaire 3, e.g. because they forget to answer or could pass away in the follow-up period. To avoid the loss of data, an intention-to-treat analysis is applied [89].

There is a risk for social-desirability bias in relation to the questionnaire [90,91], e.g., because the patients are answering what they think is expected of them. The same bias might occur during the medication review with the patients telling the Medication Coordinator what they think the Medication Coordinator requests to hear.

As hospitalized patients are often vulnerable, it can be difficult for them to answer a questionnaire. Especially if the questionnaires are long, they can be cognitively demanding. For this reason, the addition of the two VAS’s will capture patient-reported outcomes regarding quality of life and treatment burden.

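### The primary model is said to be unbiased under missing at random because it uses maximum likelihood; a population-averaged beta regression with clustered standard errors does not have that property

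*Protocol article*

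**What the plan says.** Section 2.6.1 sets the primary model: "The primary analysis will be a beta-regression with clustered standard errors as we have repeated measurements, thus adopting a population-averaged approach". The mean model has group, time and their interaction ("We will incorporate an interaction between group and time, as we are unsure if the treatment is stable over time"), with estimates at baseline, discharge and six months. The section links intention-to-treat to the need to manage missing data. It then argues from maximum likelihood that "we can assume that the beta regression will yield unbiased results if the data is missing at random or completely at random". A joint model, with logistic regression for dropout, is added for data missing not at random.

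Three other places bear on this:

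- Section 2.6.2 uses the same maximum-likelihood argument for the beta-binomial analyses of quality of life, treatment burden and medication risk score: "we will adopt the same test and manage missing data similarly to the primary analysis".
- Section 2.4 says of the sample-size simulation that "we assumed the risk of dropout after 6 months was associated with age". Age is not among the model terms named in section 2.6.1.
- Section 3 says, of the questionnaires, "To avoid the loss of data, an intention-to-treat analysis is applied".

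**The concern.** Maximum likelihood lets one ignore a missing-at-random mechanism when the likelihood is a correctly specified joint likelihood of each patient's repeated values. The observed discharge value then carries information about the unobserved six-month value. The model described has no such link. Visits are stacked as independent records, and the clustered variance repairs the standard errors without changing the point estimates. This is a working-independence estimator. It is consistent when data are missing completely at random, or when missingness depends only on terms in the mean model: group and time as named, and age if it is added.

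At stake is the six-month treatment effect and its test. If patients with a high PIM proportion at discharge are more likely to be lost, the six-month mean of those remaining is too low. If this happens differently by arm, the contrast moves too. The article names no weighting, imputation or random effect for the missing-at-random case.

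**Working it through.** **Is there a plan figure to reproduce?** The plan gives none for bias. Its 93% power cannot be rebuilt exactly: the simulation code is not shown, and the stated variance of 0.5 exceeds the largest variance a proportion with mean 10–15% can have (μ(1−μ) = 0.09 to 0.1275). An outcome SD therefore has to be assumed. Simulated beta regressions with Table 1 proportions and 70 per arm gave about 92% power at SD 0.09 without dropout, and 95% at SD 0.08. SD 0.09 is thus roughly compatible with the stated 93%.

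**Inputs from the article:** 70 per arm (section 2.4); two-sided 5% level (section 2.6); Table 1 six-month proportions of 13% and 12%, a gap of 1 point.

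**Assumed inputs:** SD 0.09; correlation ρ between visits of 0.5 to 0.8; overall dropout of 5 to 20%.

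**Illustration with no true effect.** Control dropout is completely at random. In the intervention arm, dropout is 35% above and 5% below the median earlier PIM value (20% overall). For a normal outcome:

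- Mean standardised earlier value among those retained: z = [0.5×0.65 − 0.5×0.95] × √(2/π) / 0.80 = −0.15 × 0.798 / 0.80 = −0.150.
- Bias in the six-month contrast = ρ × SD × z. At ρ = 0.7: 0.7 × 0.09 × (−0.150) = −0.0094, or −0.9 points. At ρ = 0.5 and 0.8: −0.7 and −1.1 points.
- Standard error with 56 observed per arm: 0.09 × √(2/56) = 0.0170. Bias/SE = 0.55.
- Rejection at ρ = 0.7: Φ(−1.96 + 0.55) + Φ(−1.96 − 0.55) ≈ 0.086.

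Simulations of this scenario gave the same bias, with type I error of 8.3% and 9.2% in two separate runs at ρ = 0.7, and about 7 to 10% over ρ = 0.5 to 0.8. Conditioning on the earlier value removed the bias and restored about 5%.

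**Varying the mechanism and the dropout rate (ρ = 0.7 unless stated):**

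| Scenario, no true effect | Bias in contrast (points) | Type I error |
|---|---|---|
| One arm only, 20% dropout | −0.9 | 8–9% |
| One arm only, 10% dropout | −0.4 | about 6% |
| One arm only, 5% dropout | −0.2 | about 5% |
| Same mechanism in both arms, 20% | 0.0 | 5.1% |
| Age-like driver (correlation 0.3 with PIM), both arms | 0.0 | 5.0% |
| Age-like driver, intervention arm only | −0.3 | 5.5% |

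The 10% and 5% rows follow from the same formula with 17.5% v 2.5% and 8.75% v 1.25%: z = −0.067 and −0.032, so bias = 0.063 × z = −0.0042 and −0.0020.

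**Check with an actual beta likelihood.** An independence beta regression with saturated group-by-time terms was fitted to 60,000 simulated patients per arm, with true six-month difference about 0.010 and ρ from 0.3 to 0.9.

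- Missing completely at random: 0.010, unbiased.
- Dropout depending on discharge PIM in control only: 0.014 to 0.020.
- In intervention only: 0.003 to −0.007.
- Same slope in both arms with Table 1's discharge gap (15% v 10%): 0.007 to 0.003.
- Same slope, no group difference: contrast near zero, although both arm means fell from 0.12 to about 0.105–0.115.

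Weighting by the true retention probability recovered the truth to within 0.002.

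**The case against.** The strongest case against concerns size, and much of it stands.

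- Contrast bias of about a point needs dropout that depends on earlier PIM differently by arm. With a common mechanism and no group difference the contrast is unaffected. The common-mechanism bias above relies on Table 1's discharge gap, yet section 2.2.4 says suggested amendments are not implemented before discharge.
- 20% dropout is assumed. PIM comes from medication lists, sections 1 and 2.7 point to records and registers, and section 2.2.1 names only withdrawal of consent or death as reasons for not continuing. The loss discussed in section 3 concerns the third questionnaire, so it bears on secondary outcomes.
- The 8–9% is for one unadjusted six-month test. The plan uses a global test, then adjusted z-tests. In the same scenario the global test also rejected about 9% (about 6% under completely random dropout with that statistic). A false six-month claim after the gate and an assumed Bonferroni correction over three visits occurred 2.8% of the time.

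A reader might go further and infer three things that the article does not support. First, that the main treatment comparison is biased under the age-related dropout the plan expects: acting equally in both arms, such dropout left the contrast unbiased. Second, that the joint model is offered as the only protection needed: it is offered to assess the influence of data missing not at random. Third, that age is excluded: it is not named, but the article gives no closed covariate list.

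None of this rescues the sentence, which claims the property for missing at random in general. Nor does the joint model make that claim about the primary model true.

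**Conclusion.** The concern holds as a wrongly stated property of the primary model, repeated by reference for the secondary outcomes. It is not a detail left to a fuller plan: such a plan would have to contradict the published sentence. The consequence for the treatment contrast is conditional. It runs from nil, with a common mechanism and no group difference, through about 0.4 points at 10% dropout, to about 1 point at 20% dropout when dropout depends on earlier PIM in one arm only. The last figure matches the six-month gap in Table 1. It rests on an assumed SD of 0.09 and a correlation near 0.7, and is an illustration, not a forecast. Arm-differential dropout is possible, since only intervention patients receive the medication review and the day-7 call. The wording in section 3 that intention-to-treat avoids loss of data is also wrong: it defines who is analysed and recovers no missing values.

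**What to change.** Replace the missing-at-random sentence in section 2.6.1 with a statement of what the chosen estimator requires, and make the primary analysis valid under missing at random by one of two routes:

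1. Multiply impute by arm from baseline PIM, discharge PIM and age, then fit the planned population-averaged beta regression with clustered standard errors.
2. Use a likelihood with a patient random effect and age, standardised to a marginal difference. Baseline PIM should enter either as an outcome time point or as a covariate, not both.

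Apply the same approach to the secondary outcomes in section 2.6.2. Keep the joint model as the sensitivity analysis for data missing not at random. Correct the intention-to-treat wording in section 3.

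The cost is wording and a little more analysis work. Age and PIM at the earlier visits are already collected, and the first route leaves the planned model and tests in place.
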